#### *Immunogenicity*

Responses to vaccination will be assessed by humoral and cell mediated tests. The assessment of humoral response will be by the determination of specific binding and neutralizing antibodies against the vaccine.

The qualitative and quantitative evaluations of cell mediated immunogenicity will be through the determination of interferon gamma by the ELISPOT assay; whole blood lymphocyte proliferation assay (FASCIA); intracellular cytokine staining (ICCS) using flow cytometry as well as cytotoxic T lymphocytes (CTL) assays against peptides of the different immunogens. A detailed description of safety and immunogenicity assessments is depicted below.

## SAFETY AND IMMUNOGENICITY ASSESSMENTS

### *SAFETY ASSESSMENTS*

Local and systemic assessments whether normal or abnormal will be recorded starting from 10 minutes up to 4 weeks after immunization in the following intervals: 10 and 30 minutes as direct observation after immunization, day 1-3 (at the clinic or by home visit), 2nd and 4th week at

clinic. While study personnel will use {CRF 8 (I-III)} to record all local and systemic events at the clinic, volunteers will use diary cards at home for the same. Volunteers who will not report to the study clinic within the first three days will be home visited within a week. Volunteers will be instructed to call or report to the specified study personnel immediately if any unusual or severe sign or symptom appears after immunization. These volunteers should be seen in the clinic at the time of maximal symptoms, if possible, and will be followed up clinically until resolution of symptoms.

An adverse event is any undesired, noxious or pathological change in a patient or volunteer as indicated by physical signs, symptoms, and/or laboratory changes that occurs following administration of one of the vaccines, whether or not considered vaccine related. This definition includes intercurrent illnesses or injuries, and exacerbation of pre-existing conditions.

#### **Local adverse events**

Pain in the muscle injected will be graded by the volunteer according to the criteria in the specific appendix as mild (1) moderate (2), severe (3) or serious (4) and recorded in the appropriate case record form or once the volunteer has left clinic, in the diary card. Redness and or induration will be recorded as the maximum diameter and expressed as a proportion of the arm circumference and graded on this criteria and the presence of symptoms according to the specific appendix. Arm circumference will be measured at screening, at the point one third of the way down from the acromio-clavicular joint towards the elbow joint in the injected arm. Investigating personnel will record the maximum diameter, as well as the presence of any itching or other discomfort and any medication taken for relief of symptoms. Blistering (vesiculation) or ulceration will be graded according to size, depth, time to healing and character of blisters (blood-filled).

The sole presence of an induration following intramuscular injection considered grade 3 will not be sufficient to stop the trial (see table). Clinical staff will complete the case record form following each immunisation. In the event that there are two observations on the same day, those confirmed at a visit will take precedence over diary card observations in the analysis. Study personnel should verify all grade 3 or 4 events.

#### **Systemic adverse events**

Temperature will be measured by the axillary route prior to immunisation and 30 minutes after the immunization by study personnel, and graded according to the table in **appendix xiv**. Volunteers will be given thermometers to record their temperature in the diary card on the evening of immunisation, and daily thereafter for 7 days, and if still raised, they will be advised to continue to monitor their temperature daily until it returns to normal. The temperature observed by the clinical team will be recorded in the case record forms for visits. In case of grade 3 and 4 fever, malaise, chills/rogors and headache, and where indicated, additional tests to exclude other common causes of fever like malaria will be performed.

Chills, headache, nausea, vomiting, malaise and myalgia will be graded by the volunteers according to **appendix xiv**, recorded in the diary card on the evening following immunization and daily for 7 days, or until resolution of symptoms whichever is longer. On days where a visit coincides with the diary card, the clinical staff will collect the information directly and record it on the case record form, and this will take precedence over diary card entries in the analysis. Study personnel will verify all grade 3 or 4 events.

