## END POINTS

### Primary

#### *Safety*

The safety of immunization with the seven DNA plasmids carrying HIV-1 genes will be assessed by *clinical features as well as standard biochemical and haematological laboratory tests*. Any worsening of the severity grade will be considered for causality with the vaccine.

The alternative routes of immunization (intramuscularly and intradermally with the Bioject device) will be evaluated by assessing local (pain, cutaneous reactions including induration), general (fever, chills, headache, nausea, vomiting, malaise, myalgia) and other unsolicited adverse events on vaccination day and within 7 days. Any grade 3 or 4 event will be taken as an indication that the arm is less tolerable.

The primary safety parameters will be graded according to *appendix xiv*, and are:

1. Local adverse event Grade 3 or above (pain, cutaneous reactions including induration)
2. Systemic adverse event Grade 3 or above (temperature, chills, headache, nausea, vomiting, malaise, and myalgia)
3. Other clinical or laboratory adverse event Grade 3 or above confirmed at examination or on repeat testing respectively

Tests for possible toxicity due to vaccination will include: Liver function tests, renal function tests and full blood picture. Any event attributable to vaccine leading to discontinuation of the immunization regimen must be documented.

Data on local and systemic events listed above will be solicited with specific questions or using a diary card for a minimum of 7 days following each immunization. Data on other clinical events and laboratory events will be collected with an open question at each visit and through routine scheduled investigations respectively.

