### **Safety data**

The number and percentage of subjects experiencing any adverse events (AE), grade 3 or 4 adverse events, serious adverse events (SAE), and the number of events reported, will be summarized by severity and reported relationship to study treatment for each treatment group, both for all adverse events and by type of adverse event. Calculation of incidence rates of adverse events will include each subject only once, either according to worst severity or first reported event.

Rates of the various adverse events will be compared between the study arms using Fisher's exact test. Rates will be summarized using exact binomial confidence intervals

Safety haematological and biochemical laboratory parameters will be summarized at each study visit according to study arm. Comparisons will be done using 2-sample t-tests or non-parametric equivalents as appropriate to the data

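### Clinic-over-diary precedence and an open worst-or-first counting rule can remove a volunteer's worst reaction, so grade 3 or higher rates can be understated

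*Protocol*

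**What the plan says.** Two rules in the Protocol are involved.

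**Same-day precedence.** Under Local adverse events, when a day has two observations, "those confirmed at a visit will take precedence over diary card observations in the analysis". Under Systemic adverse events, when a visit falls on a diary day, staff collect the information directly "and this will take precedence over diary card entries in the analysis". That second sentence follows the list running from chills to myalgia. Temperature has its own paragraph and is not expressly named.

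**Timing of the two sources.** Safety Assessments sets clinic checks at "10 and 30 minutes as direct observation after immunization", followed by a contact on day 1-3. Mode of Vaccine Delivery puts any reaction seen at 30 minutes on the case record form. The systemic symptoms are "recorded in the diary card on the evening following immunization and daily for 7 days".

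**Counting.** The Safety data section says: "Calculation of incidence rates of adverse events will include each subject only once, either according to worst severity or first reported event". It gives no rule for choosing between the two. The same section also summarises subjects with grade 3 or 4 events, and tabulates both overall and by type of event.

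End Points makes grade 3 or above, local or systemic, a primary safety parameter, and takes any single grade 3 or 4 event as a sign that the arm is less tolerable.

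**The concern.** A precedence rule is sensible when staff and volunteer report the same symptom at about the same time. Here the two readings on an injection day are hours apart and the staff reading comes first. If the rule is programmed as written, a grade 0 or 1 at 30 minutes stands for the day and a grade 3 that evening drops out.

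Counting by first reported event can act in the same direction. With five injections over 80 weeks, a volunteer's first fever may be mild and a later one severe.

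Both rules bear on the primary safety parameters. With 20 volunteers in each active arm and a one-event tolerability criterion, a single lost volunteer can change how an arm is described.

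**Working it through.** The protocol states no expected grade 3 rate, power or effect size for safety, so there is no figure to reproduce. The check is a reading of the text followed by illustrations on stated assumptions.

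**1. Injection day.** The clinic record is made at 10 and 30 minutes and the diary entry that evening. Both carry the same date, so the condition for precedence is met. The clinic value is always the earlier one. A reaction that develops after the volunteer leaves can be recorded the same day only in the diary or through an unscheduled call or visit.

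**2. Day 1-3 contact.** The same conflict arises if the volunteer worsens after the contact. It can also go the other way: if the clinic grade is the higher, precedence raises the analysed grade.

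**3. Counting rule.** Under worst severity nothing is lost. Under first event, a later and worse grade of the same event type is hidden in the by-type table, and a later and worse grade of any type is hidden in the pooled table.

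**4. What a lost record does in an arm of 20.** Let p be the assumed true proportion of volunteers with a grade 3 or higher event, and f the assumed share of them whose only such record is dropped. The chance that the arm shows at least one is 1 − (1 − p(1 − f))^20.

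| p | f = 0 | f = 0.25 | f = 0.50 | f = 0.75 |
|---|---|---|---|---|
| 5% | 64.2% | 53.4% | 39.7% | 22.2% |
| 10% | 87.8% | 79.0% | 64.2% | 39.7% |
| 20% | 98.8% | 96.1% | 87.8% | 64.2% |

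For scale, the exact 95% interval is 0 to 16.8% for 0/20 and 0.1 to 24.9% for 1/20.

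**5. First against worst over five injections.** Assume a grade 3 or higher probability of 2% per injection, a reaction of any grade at a proportion q of injections, and independence between injections. This applies within one event type, or to the pooled table.

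- Worst severity: 1 − (1 − 0.02)^5 = 9.6%.
- First event: (0.02/q)(1 − (1 − q)^5) = 4.6%, 3.3% and 2.5% for q = 0.4, 0.6 and 0.8.
- Extreme case, a reaction at every injection (q = 1): 2% by first event against the same 9.6%.

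These figures show direction and sensitivity only. Neither f nor q can be obtained from the protocol.

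**The case against.** The best defence is that the override on injection day is only one reading. The systemic sentence speaks of staff collecting the information directly, and staff cannot collect the evening's symptoms at 30 minutes. The local sentence favours what is confirmed at a visit, and an early check confirms nothing about the evening. Several safeguards also exist: a nurse contact the next day or within three days, a 24-hour telephone line, review of diaries at later visits, staff verification of all grade 3 or 4 events, reporting of such events to the DSMB within 2 working days, and the separate grade 3 or 4 summary.

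This has force. The safeguards are aimed at exactly the events at risk and should recover some of them. But no text says that they overrule the precedence sentences. Verification, for example, is required without stating that a verified diary grade is kept over a lower clinic grade from the same day.

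Four stronger inferences should be resisted:

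- **That the rates are understated.** The text supports only that they can be. The override needs two same-day sources, can raise a grade, and leaves diary entries on days without a visit intact.
- **That 60 × 5 = 300 evening entries are overridden.** That product is the number of injection days on which both sources could exist. It is not a count of replaced grades.
- **That the diary is the only record until the next day.** It is the scheduled same-day record, but interviews and calls can capture the reaction too.
- **That grade 1 pain after the first DNA injection would hide grade 3 fever after the second MVA injection.** By event type the fever still appears as grade 3, and the grade 3 or 4 summary is separate. Only the pooled table could show grade 1, and only if first event were chosen.

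A statistical analysis plan may settle the worst-or-first choice. The protocol nevertheless writes the alternative in, so its wording should be corrected.

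**Conclusion.** The point holds in a limited form. As written, clinic precedence can replace a later, worse diary grade on injection days and on the day 1-3 contact day, and the counting rule permits a choice that hides later, worse grades of the same type or in the pooled table. Grade 3 or higher rates can therefore be understated. For systemic symptoms the precedence wording reaches chills to myalgia and does not expressly reach temperature.

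The size is unknown. On the assumed inputs above, the effect on whether an arm of 20 shows any grade 3 or higher volunteer runs from slight (98.8% to 96.1% at p = 20%, f = 0.25) to large (64.2% to 22.2% at p = 5%, f = 0.75). The counting fault is the unfixed choice; if worst severity is used, that rule costs nothing.

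**What to change.** **Local and Systemic adverse events.** Replace both precedence sentences with one rule: clinic and diary entries are both kept, and for each volunteer, injection and symptom the analysis uses the highest grade recorded from either source. Flag grade 3 or 4 events that the clinic has verified, and lower a diary grade of 3 or 4 only with a documented reason. State whether the rule covers temperature.

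**Safety data.** Delete the first-reported-event alternative and count each subject once at worst severity.

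**Cost.** Wording and programming only, because the diaries and case record forms already hold both values. Reported rates may be slightly less favourable. The change should be made before unblinded analysis.

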### **Other adverse events**

These will be recorded as reported following an open question to volunteers, with the dates of commencement and resolution, and any medication required. They will be graded according to the general principles outlined in *appendix xiv*. Social harm will also be recorded as an adverse event, graded according to the general guidelines (which include denial of health and life insurance, employment, immigration and marriage relationships). All grade 3 or 4 events will be verified by study personnel.

### **Routine laboratory parameters for safety assessments**

The following safety assessments will be undertaken at appropriate laboratories in MUHAS according to standard operating procedures.

#### *Haematology*

Haemoglobin; white blood cell count, total and differential counts, specifically granulocytes and lymphocytes; platelet count and red blood cell counts.

#### *Clinical chemistry*

Liver function tests (ALT, bilirubin total and direct), and serum creatinine and blood glucose.

#### *Immunology*

Determination of CD4 counts and percentage  
Syphilis (VDRL, and when necessary TPHA)  
Screening for HBsAg

#### *Other tests*

ECG will be done at MVA vaccination and two weeks after the MVA vaccination. It will also be done at anytime whenever a volunteer comes with symptoms and signs suggestive of perimyocarditis.

#### *Troponin test*

Serum for a later troponin test will be collected

The following assessment will be undertaken on a specimen of urine, conducted by a member of the study staff according to trial specific standardised operating procedures:

#### *Urinalysis*

Dipstick conducted by clinical staff and recorded normal/abnormal. If abnormal a mid-stream urine specimen will be collected in order to grade the event according to *appendix xiv*.

All grade 3 or 4 adverse events or serious events and/or those that necessitate a physician's visit or are treated with a prescribed medication will be evaluated. The volunteer will be followed carefully until the condition is resolved and/or the cause is identified. Any medication or other therapeutic measure taken to relieve symptoms of the medical problem must be recorded on the appropriate case report form page(s) in addition to the outcome of the adverse event. Where a diagnosis is possible, it is preferable to report this rather than a series of terms relating to the diagnosis. When reporting a syndrome, the associated signs and symptoms will be parenthetically indicated following the syndrome rather than as separate event.

### **Cellular responses**

The assessment of primary cellular responses will be achieved by determining the following HIV-1 specific cellular immune responses:

- CD8 and CD4 T helper cell responses
  - IFN- $\gamma$  ELISPOT and Interleukin-2 assay (on stored Peripheral Blood Mononuclear Cells (PBMC's)), including determination of cross clade responses, using pools of overlapping peptides representing env, gag and pol proteins
  - Intracellular cytokine staining (ICS) for IFN- $\gamma$  and Interleukin-2 (IL-2) (ref 27) using the same peptide pools as in the ELISPOT and testing both for CD8 and CD4 T cell responses
- CD4 T helper cell responses
  - Lymphocyte proliferation assay (LPA) to the immunizing antigens and mitogens on fresh PBMC's
    - Standard assay: measurement of proliferation by uptake of  $^3\text{H}$ -thymidine
    - New assay: whole blood flow-cytometric assay (FASCIA=Flow-cytometric Assay of Specific Cell-mediated Immune response in Activated whole blood) developed at SMI. Both CD4 and CD8 T cell responses can be demonstrated by this method.
- CD8 T cell response
  - Cytotoxic T lymphocytes (CTL) by chromium release assay

Interferon-gamma Enzyme-linked immunospot (ELISPOT) will be used as a standard assay to monitor HIV cellular immune response in vaccinated individuals and will be performed on fresh PBMC's. These procedures will be validated prior to the trial. Individuals with <50 SFC/million PBMCs will be regarded as non-responders. If the average value of sample wells is >4 times the

background (medium only) and >55 SFC/million PBMCs the individuals will be regarded as responders.

A new whole blood flow-cytometric assay (FASCIA=Flow-cytometric Assay of Specific Cell-mediated Immune Response in Activated whole blood) developed at SMI will also be performed later on stored PBMCs. Both CD4 and CD8 T cell responses can be demonstrated by this method. Quality control and exchange of specimens with international laboratories will be performed.

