### **The on-going Phase I/II trial (HIVIS03) in Tanzania**

The HIVIS03 trial is now fully enrolled with the required 60 volunteers, all of whom came from the Police Force. 15 (25%) of them are females. Attendance at the scheduled follow up visits has so far been excellent. As of 19th May 2008 a total of 57 volunteers had already received the 3 DNA/Placebo vaccinations, and the immunogenicity data has shown very good results, with 19 out of 46 (41.3%) exhibiting responses by interferon gamma ELISPOT. A total of 26 volunteers have received their first MVA/placebo vaccination, and these have all not been associated with any untoward side effect.

Generally speaking, the vaccines have been very safe, and to date we have had 3 SAE's which are all unrelated to vaccination.

It is unfortunate that it was not possible to obtain MVA for the second boost in time to continue with MVA boosting as per earlier protocol. This was due to production difficulties at the WRAIR. These problems have now been solved, as a dedicated Contractor has been hired to carry on with the assignment of MVA production. The person in charge of the original production of the vaccine for the 1st boost, [name] [name], now works for that company. Hence the MVA vaccine is now expected to be available in Tanzania during October- November 2008. Indeed this amendment takes a further minor delay into account.

It is reassuring to note that so far the candidate vaccines being used in HIVIS 03 have been very safe as expected, and that the delay in providing a second MVA boost is not expected to negatively influence the safety or Immunogenicity results.

Furthermore, additional funds have been secured to cover the extension of study activities from the European and Developing Countries Clinical Trials Partnership (EDCTP) as one of the work packages under the Tanzania and Mozambique Vaccine (TaMoVac) programme for the period 2008 to 2011.

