#### *The primary end-points are:*

1. The safety of immunization with the seven DNA plasmids carrying HIV-1 genes as assessed by clinical signs, and standard biochemical/haematological laboratory tests where any worsening of the severity grade will be considered for causality by the vaccine

2. A qualitative and quantitative evaluation of the magnitude and quality of humoral (neutralizing and binding antibodies, by serology) as well as cellular (cytotoxic T-cell, IFN-gamma by ELISPOT, T-cell proliferation (Fascia) and intracellular cytokines by flow cytometry) immune responses as elicited by the different schedules of immunization

The alternative routes of immunization (im and id with the Bioject device) will be evaluated for adverse events by assessing local (pain, cutaneous including induration), general (fever, chills, headache, nausea, vomiting, malaise, myalgia) and other unsolicited adverse events within 7 days. Any grade 3 or 4 event will be taken as an indication that the arm is less tolerable

*The secondary endpoints are:*

1. A qualitative and quantitative assessment on the presence of necessary infrastructure and human capacity to conduct HIV-related vaccine studies at MUHAS.

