### **Immunogenicity Data**

Immunogenicity endpoints will be compared formally at week 0, 10 and 12, according to study dosing group. Binary endpoints will be compared using Fischer's exact test. Continuous endpoints will be compared using 2-sample t-tests or non-parametric equivalents as appropriate to the data.

Immunogenicity of the candidate vaccine will be determined based on comparisons between study treatment arms. Associations between immunogenic endpoints will be assessed using multivariate regression models.

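### The ELISPOT responder and non-responder rules are not complements, so some volunteers with a valid result have no class for the binary comparison

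*Protocol*

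**What the plan says.** The protocol's section on cellular responses says that interferon-gamma ELISPOT "will be used as a standard assay to monitor HIV cellular immune response in vaccinated individuals". It then gives two separate decision rules.

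- Non-responder: "Individuals with <50 SFC/million PBMCs will be regarded as non-responders".
- Responder: "If the average value of sample wells is >4 times the" "background (medium only) and >55 SFC/million PBMCs the individuals will be regarded as responders" (one sentence, broken across a page; both conditions must hold).

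That section gives no default class, indeterminate category or retest rule, and none appears elsewhere in the protocol.

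Three other places determine how the classification is used:

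- The list of primary endpoints includes, within the second one, "cellular (cytotoxic T-cell, IFN-gamma by ELISPOT, T-cell proliferation (Fascia) and intracellular cytokines by flow cytometry) immune responses", alongside the antibody measures.
- Under Immunogenicity Data, "Binary endpoints will be compared using Fischer's exact test". Continuous endpoints are compared by t-tests or non-parametric equivalents.
- The section on the ongoing trial already reports the assay as a proportion, "with 19 out of 46 (41.3%) exhibiting responses by interferon gamma ELISPOT".

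The Statistical analysis section bases analyses on intention-to-treat.

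**The concern.** A two-class test needs a rule that places every valid result in one of two classes. Here the class boundaries are written twice, with different count cut-offs (50 and 55) and with a background condition on one side only. A result that is not below 50 can still fail the responder test, and the protocol does not then say what it is.

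The cases left open are the ones most open to argument: borderline counts, and high counts on a high background. If they are left out, the denominator shrinks while the number of responders stays the same, so the response rate rises. If they are assigned later, the choice is made once results are known. In arms of 20, either can change a Fisher p-value noticeably.

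**Working it through.** **Inputs.** The two rules come from the section on cellular responses. The arm sizes (20 in each active arm) come from the Study Design table in the Synopsis. No power or sample-size figure is involved. The one reported proportion reproduces: 19/46 = 41.3%.

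**Step 1: the unclassified set.** Let S be the average of the sample wells in SFC/million and B the medium-only background on the same scale.

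- Non-responder: S < 50.
- Responder: S > 55 and S > 4B.
- Neither: S ≥ 50 and (S ≤ 55 or S ≤ 4B).

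The unclassified set is therefore {50 ≤ S ≤ 55} together with {S ≥ 50 and S ≤ 4B}. The second part needs B ≥ 50/4 = 12.5 and has no upper limit on S. No result can be in both classes, since S < 50 and S > 55 exclude each other. Enumeration over S = 0 to 500 and B = 0 to 100 agreed with this description at every point.

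| S | B | S/B | Class as written |
|---|---|---|---|
| 49 | 5 | 9.8 | non-responder |
| 50 | 5 | 10.0 | none |
| 55 | 5 | 11.0 | none |
| 56 | 5 | 11.2 | responder |
| 60 | 15 | 4.0 | none |
| 60 | 14 | 4.29 | responder |
| 200 | 60 | 3.33 | none |

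**Step 2: effect on a response rate.** With r responders among n valid assays, k of them unclassified, the rate is r/n if the k count as non-responders and r/(n − k) if they are dropped. The second is larger whenever r and k exceed zero. As an assumption, suppose all valid assays were in the reported denominator and two of the 46 were in the gap. The figure would then be 19/46 = 41.3% or 19/44 = 43.2%. The protocol does not say how that denominator was formed.

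**Step 3: effect on the Fisher comparison.** All counts here are assumed, because the documents give none. Arm II is held at 16/20. Arm I has the clear responders and unclassified volunteers shown. P-values are two-sided.

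| Arm I clear responders | Unclassified | Counted as non-responders | Dropped | Counted as responders |
|---|---|---|---|---|
| 8 | 1 | 8/20, p = 0.0225 | 8/19, p = 0.0225 | 9/20, p = 0.0484 |
| 8 | 2 | 8/20, p = 0.0225 | 8/18, p = 0.0424 | 10/20, p = 0.0958 |
| 9 | 1 | 9/20, p = 0.0484 | 9/19, p = 0.0484 | 10/20, p = 0.0958 |
| 9 | 2 | 9/20, p = 0.0484 | 9/18, p = 0.0869 | 11/20, p = 0.1760 |

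The last column is the least plausible handling, since these volunteers fail the stated responder test. Even without it, the last row shows that dropping two volunteers, rather than keeping them as non-responders, moves p from below to above 0.05.

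**The case against.** The strongest reply is that the responder class is fully defined, so anyone who fails it is naturally not a responder. Intention-to-treat points the same way, and the reported 19 of 46 mentions no third category. On that reading nothing is undefined. It is a sensible reading, and it is the one the fix adopts. But it makes the explicit below-50 sentence redundant, and the text does not state it. Nor can the gap be taken as a deliberate grey zone: a grey zone would need a name and a stated handling, and it would not explain why a count of 200 on a background of 60 has no class.

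A second reply is that an analysis plan may settle this. That would hold if the protocol had left the definition open. It did not: it wrote one, and any analysis plan would have to add to it or override it.

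A third reply is that laboratory staff are blinded to regimen, so a late assignment should not be steered by arm. This stands, and it limits the risk of deliberate bias. It does not remove the dependence of the result on an unstated choice.

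Two stronger readings are tempting, and the documents support neither.

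- A reader might infer that the primary immunogenicity endpoint as a whole is undefined. It is a broad evaluation across several antibody and cellular assays, and ELISPOT responder status is one component. The continuous analyses do not use the classification.
- A reader might infer that testing env, gag and pol peptide pools leaves the false-positive rate uncontrolled. The protocol gives neither a number of pools nor a per-pool rate, and the way pools combine into one call is commonly left to an analysis plan or laboratory procedure. False positives unrelated to vaccine would also affect the placebo arms, diluting the contrast between arms and not inflating its type I error.

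**Conclusion.** The point holds as a defect in a stated decision rule. The two ELISPOT rules leave without a class every volunteer with 50 to 55 SFC/million, and every volunteer with 50 or more at no more than 4 times background. This follows from the text alone and rests on no assumption. That responder status will be analysed as a binary endpoint is an inference, though a firm one, from the responder wording, the planned Fisher's test and the proportion already reported.

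The size is unknown. The documents do not say how many volunteers fall in the gap, so the p-values above show only what is possible with 20 per arm. If no volunteer falls in the gap, nothing changes. If one or two do, their handling can decide which side of 0.05 a close comparison lands on. The defect is limited in scope and cheap to cure, and should be cured before the responder analysis is run.

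**What to change.** Keep the responder definition as it stands (more than 4 times background and more than 55 SFC/million). Replace the below-50 sentence with: all other volunteers with a valid assay are non-responders. The unclassified set is then empty, the protocol's own responder thresholds are unchanged, and every valid assay stays in the denominator, in line with intention-to-treat.

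The cost is one clause and no new data. The downside is that response rates may be slightly lower than if borderline and high-background results were left out.
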